**Table 2 Tab2:**
[figure not shown]
Schedule of enrolment, interventions, and assessments

The design of this clinical trial has strong and significant factors, such as the control group being exposed to the same number of hours and consecutive days of the protocol which means that the intensity and volume of training for both groups are similar. The similarity in the assessment of follow-up outcomes and the blinded evaluation for both groups is also a strong point of the trial’s design.

Another important aspect of our methodology is that we follow the initial proposal of the group that developed the protocol. It is important to clarify that when we first put this protocol into practice, we maintained the first study published by the group. At that time, the protocol was performed with 15 days of intervention [25]. Following information updates about the protocol from [name] and colleagues at the University of Alabama in Birmingham to use 10 days of training, we decided to continue with the initial methodology plan as the protocol is still evolving and, in this way, offers us an opportunity to discuss the optimum amount of LE-CIT.

In conclusion this is the first clinical trial that proposes to evaluate whether the LE-CIT protocol can improve gait and balance outcomes, and whether these gains can be transferred to daily life activities. If our findings are positive, we will be able to suggest that this protocol may be better than the conventional intensive physiotherapy. However while intensity in rehabilitation is important, its transference to the real world and activities relevant to daily life may be even more valuable.

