**Methods:**

The study adopts a randomized, controlled, single-blinded study design. Forty-two patients, who suffered a stroke, who were in the chronic phase of recovery (>6 months), with gait disability (no community gait), and who were able to walk at least 10 m with or without the advice or support of 1 person, will be randomly allocated to 2 groups: the LE-CIT group or the control group (intensive conventional therapy). People will be excluded if they have speech deficits that render them unable to understand and/or answer properly to evaluation scales and exercises selected for the protocol and/or if they have suffered any clinical event between the screening and the beginning of the protocol. Outcome will be assessed at baseline (T0), immediately after the intervention (T1), and after 6 months (T2). The outcome measures chosen for this trial are as follows: 6-min walk test (6minWT), 10-m walk test (10mWT), timed up and go (TUG), 3-D gait analysis (3DGA), Mini Balance Evaluation Systems Test (Mini-BESTest), and as a secondary measure, Lower Extremity Motor Activity Log will be evaluated (LE-MAL). The participants in both groups will receive 15 consecutive days of daily exercise. The participants in the LE-CIT group will be submitted to this protocol 2.5 h/day for 15 consecutive days. It will include (1) intensive supervised training, (2) use of shaping as strategy for motor training, and (3) application of a transfer package (plus 30 min). The control group will receive conventional physiotherapy for 2.5 h/day over 15 consecutive days (the same period as the CIT intervention). Repeated measures analyses will be made to compare differences and define clinically relevant changes between groups.

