#### Intervention group (LE-CIT)

The participants in this group will be submitted to physiotherapy 3 h/day for 15 consecutive days. The physiotherapy will be divided into 2 parts: the first 30 min will be dedicated to the transference package and 2.5 h of intensive training. The CIT protocol is composed of [16]:

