Shaping—method based on principles of behavioral training in which the motor or behavioral aim is approached in small steps by successive approximation, which means that the task may be hampered by the patient’s motoric capacities or may stimulate the patient to perform the same activity faster. Every functional task is performed 10 times and feedback is given on each attempt. This activity is chosen from the shaping bank considering (a) specific articular movement where the main deficit lies, (b) the joint movement that is believed to have potential for improvement, and (c) preference for associating tasks that have a similar potential to produce specific improvements. Each shaping program is individualized and has 8–12 tasks selected from the shaping bank. However, new tasks may be created for each participant to improve their motor deficits. For instance, to improve weight-bearing on the paretic side you can ask the patient to move the non-affected limb to touch “X”s placed on the floor in front of their feet, to the side, and forward while standing. The therapist can record how many cycles the patient can complete over 30 or 45 s. When it gets easier (i.e., the quantity of completed cycles increases), the therapist can place the “X” a bit further away, or increase the balance demand (by reducing the base of support, or replacing the stable surface for an instable one such as a foam).*Behavioral strategies of adherence (transference package):* These are strategies used to improve adherence through *Monitoring, Problem solving, and Behavioral contract.*○ *Monitoring:* This involves strategies which lead the patient to observe and document their performance (activity mode, duration, frequency, effort perception, and physiological answer to the activity) through LE-MAL and home diary.○ *LE/MAL and home diary:* In the daily administration of LE/MAL the patient answers questions about the participation of the impaired limb in daily activities, the period of reference being “from the last time that I asked you”.○ *Problem solving:* The LE-MAL and home diary checking provides an opportunity to discuss which barriers were encountered when using the impaired limb in real life situations and to use this information to then find solutions (environmental and task adaptation). It has to be done every day during the protocol.○ *Behavioral contract*: This is a formal agreement between the therapist, patient, and caregiver made on the first day. At this moment, the patient is committed to using their impaired limb during specific daily activities.○ *Homework*: Patients choose 10 activities on the second day that they are going to try to perform at home: 5 that they believe will be easy to achieve and 5 that they believe will be more challenging. This list must be completed in about 30 min and will be revised during the first 30 min on the next day, every day during the protocol. For each activity, they must check if it was done or not, if they do not perform their task they must write (in the comments space) the reason for not completing the task. They are requested to conduct all the tasks listed; however, they are informed that they must complete at least 70% of the list. It is worth emphasizing that the homework list is part of the behavioral package which means transference of learned movements during therapy to daily life (within functional tasks).○ *Schedule*: In this schedule the patient writes down the time spent on each activity in the list and how long they rested for.

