
#### Control group

The participants in this group will receive physiotherapy for 2.5 h/day over 15 consecutive days (the same period as the CIT intervention). The physiotherapist responsible for this group is experienced in stroke rehabilitation and has been working in this area for 10 years.

This conventional training can be defined as intervention without technological resources, using handling, verbal commands, positioning, gait training and/or pre-walking activities such as climbing stairs, balance training, lower limb strengthening, and other exercises that require standing and shifting weight to the impaired side [29].

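### The Discussion claims equal hours in both arms, but the schedules give LE-CIT 45 h of contact against 37.5 h for control, plus home tasks; only supervised training time and days are matched

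*Protocol article*

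**What the plan says.** The Discussion, in its paragraph on the strengths of the design, cites strong factors "such as the control group being exposed to the same number of hours and consecutive days of the protocol", and draws the inference "which means that the intensity and volume of training for both groups are similar".

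The two schedules in the Methods read:

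- Intervention group (LE-CIT): "The participants in this group will be submitted to physiotherapy 3 h/day for 15 consecutive days". The same section splits the session: "the first 30 min will be dedicated to the transference package and 2.5 h of intensive training".
- Control group: "The participants in this group will receive physiotherapy for 2.5 h/day over 15 consecutive days".

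The Abstract gives LE-CIT as "The participants in the LE-CIT group will be submitted to this protocol 2.5 h/day for 15 consecutive days" and then lists "application of a transfer package (plus 30 min" among the components. It gives control 2.5 h/day for 15 days.

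The homework item in the LE-CIT section has patients choose 10 activities on day 2 to try at home. The list is reviewed at the start of each following session, and at least 70% of it is to be done. On time, it says "This list must be completed in about 30 min". The safety section notes that the CIT group's homework can be done standing. No home programme is described for control.

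**The concern.** The Discussion speaks of the hours of the protocol without restriction, yet the two arm descriptions give different daily hours, and both call those hours physiotherapy. Read together, they cannot all be right.

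The protocol's own argument gives the point weight. The Background faults earlier lower-limb studies because, among other things, their control groups did not train at the same intensity, so matched dose is part of how this trial sets itself apart. The Discussion also says that larger doses of physical therapy bring significant benefit for motor function. On that premise, extra contact and home practice are a rival explanation for a favourable result. If results are presented beside an unqualified claim of equal hours, readers will take a difference as due to the content of LE-CIT with dose held constant, which the schedules do not provide.

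**Working it through.** **Inputs**

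| Quantity | LE-CIT | Control | Source |
|---|---|---|---|
| Total session per day | 3 h | 2.5 h | Intervention group; Control group |
| Supervised training per day | 2.5 h | 2.5 h | same |
| Transfer package per day | 0.5 h | none described | Intervention group; Abstract |
| Days | 15 | 15 | same |
| Home list | 10 activities from day 2, about 30 min, at least 70% | none described | Intervention group (homework item) |

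**Step 1. The stated figure.** The Discussion implies a difference of 0 h. Hours per arm = hours per day × days.

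- LE-CIT: 3 × 15 = 45 h
- Control: 2.5 × 15 = 37.5 h
- Difference: 45 − 37.5 = 7.5 h; 7.5 / 37.5 = 20%

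Equal hours are not reproduced from the Methods.

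**Step 2. The Abstract as a cross-check.** LE-CIT (2.5 + 0.5) × 15 = 45 h; control 2.5 × 15 = 37.5 h. The same totals result.

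**Step 3. What is equal.** Supervised training is 2.5 × 15 = 37.5 h in each arm, and both arms have 15 consecutive days. The 7.5 h difference is exactly the transfer package: 0.5 × 15 = 7.5 h.

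**Step 4. Home tasks (assumption).** The text does not fix this time. The 30 min may mean carrying out the tasks or filling in the list. Taking it as practice time, and letting the share of items completed stand for the share of time:

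| Days | Completion | Home time | LE-CIT total | Excess over 37.5 h |
|---|---|---|---|---|
| 13 | 70% | 0.5 × 13 × 0.7 = 4.55 h | 49.55 h | 12.05 h (32%) |
| 14 | 100% | 0.5 × 14 = 7 h | 52 h | 14.5 h (39%) |
| 15 | 100% | 0.5 × 15 = 7.5 h | 52.5 h | 15 h (40%) |

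The range is about 32% to 40%. Fifteen days is an outer bound, since the activities are chosen on day 2. If the 30 min refers to filling in the list, practice time is unknown and this range does not apply. The 20% contact difference does not depend on this.

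**The case against.** **The Discussion is really about training, and training is equal.** This is largely right in substance. The inference names training, supervised training is 37.5 h per arm, and the days match. The transfer package is described as monitoring, problem solving, a contract and homework review, so the 20% is extra contact and not 20% more supervised exercise. But the premise of the sentence is hours of the protocol, with no limit to supervised training, and home tasks that can be done standing are practice of some kind. The claim needs narrowing; it is not wholly false.

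**The transfer package belongs to LE-CIT.** This stands. The research question compares LE-CIT with intensive conventional therapy. A reader might infer that unequal time invalidates the trial. It does not: the randomized comparison of the whole package with conventional therapy remains valid.

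**The planned conclusion does not claim equal volume.** Correct. The closing paragraph says only that LE-CIT may be better than conventional intensive physiotherapy. A reader might take this as superiority at similar volume because the equality claim comes shortly before it, but the document does not write that.

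**The Abstract and Methods might seem to disagree on LE-CIT hours.** They do not. The Abstract's 2.5 h plus its separate 30 min gives the 3 h of the Methods.

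**All participants must be available 3 h per day.** That criterion, under Population, concerns availability. The Abstract and the Control group section both give control 2.5 h/day. The latter's remark that the period is the same as for CIT fits the shared 15 days and does not make the hours equal.

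**The schedules are openly stated.** They are, and no outcome, sample size or analysis step rests on the Discussion sentence. This lowers the severity but leaves the inconsistency.

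**Conclusion.** The concern holds in a limited form. The Discussion's unqualified claim of equal hours contradicts the protocol's own schedules: 45 h against 37.5 h, which is 7.5 h or 20% more scheduled therapist contact in LE-CIT. That figure needs no assumption. Adding home practice gives about 32% to 40%, but only if the 30 min is practice time, on 13 to 15 days at 70% to 100% completion. It should not be quoted without those conditions.

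A benefit could be attributed to the LE-CIT package, but not to its content at equal total volume, because content is confounded with added contact and home practice. The documents do not show how much the extra time would change the 6-min walk test or the Mini-BESTest, so no bias of a given size can be claimed. This is a correction to a stated design strength and to later interpretation; it is not a defect in the randomized comparison.

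**What to change.** 1. Reconcile the Discussion paragraph on design strengths with the Intervention group and Control group sections. Which schedule is right is for the trial team to state. If both stand, limit the equality statement to supervised training time and number of consecutive days.
2. Report therapist-contact, supervised-training and home-task time by arm. Part of this exists already: the schedule item of the transfer package has LE-CIT patients write down the time spent on each listed activity and their rest. Session time in both arms would need a simple log if it is not already kept.
3. Word the conclusion as the LE-CIT package, including its additional contact and home practice, versus conventional intensive therapy.

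The cost is a few text corrections and possibly a log sheet. The downside is that both the stated design strength and the conclusion become narrower.

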### Assessment of safety and adverse events

The main risks that the patient may be exposed to are related to the intensity of the protocol (fatigue and falls). Tiredness can be minimized by greater rest intervals between exercises if the patient shows fatigue. Regarding the risk of falls in exercises involving dynamic balance and gait training, we use a safety belt that is a device placed on the patient’s waist that facilitates the maintenance of standing posture in case of imbalance. For patients in the CIT group (who receive a homework list that can be carried out standing), responsible caregivers will be advised to wear this same belt at home (which will be provided as a loan on the first day of the protocol). Moreover, caregivers will receive very specific guidance on how to assist these patients at home during these tasks. Any adverse event must be reported on patients’ medical record, to ethical committee and in the clinical trial paper.

## Data Availability

The datasets used and analyzed during the trial are available from the corresponding author on reasonable request.

## Abbreviations

LE-CIT: Lower extremity constraint-induced movement therapy
CIT: Constraint-induced movement therapy
T0: Baseline
T1: Immediately after the intervention
T2: 6 months’ follow-up
6minWT: 6-min walk test
10Mwt: 10-m walk test
TUG: Timed up and go
3DGA: 3-D gait analysis
Mini-BESTest: Mini Balance Evaluation Systems Test
LE-MAL: Lower Extremity Motor Activity Log
GDI: Gait Deviation Index
GVS: Gait Variable Scores
GPS: Gait Profile Score
TD: Typically developing
MDC: Minimal detectable change
StP: Stance phase
SwP: Swing phase
